### Collection of patient centred outcome measures

Patient centred outcomes will be measured at baseline and annually by self-administered postal questionnaire. OHRQoL will be measured using the OHIP-14 [13]. A standardised measure of health status (EQ-5D-3 L) will be included to enable calculation of QALYs and conduct of the cost utility analysis. Patient dental anxiety status will be measured using recognised and validated psychological inventories [14, 15]. Annual patient questionnaires will also include questions relating to patient oral health related knowledge, attitudes and reported behaviours, satisfaction with dental care, and use of and reasons for use of dental services throughout the trial follow-up period.

### Collection of economic measures

The costs of all dental treatment provided by NHS dentists to patients, including the costs of planned check-ups are captured through the routinely collected data held by Information Services Division (ISD) in Scotland, NHS Information Centre, business services authority (BSA) in England and Health and Social Care Business Services Organisation (HSCBSO) in Northern Ireland. Time, travel and treatment costs associated with visits to the dentist will be collected through baseline questionnaires administered to trial participants on entry to the trial. Private dental care and use of other NHS services for dental issues are also collected by patient questionnaire.

Benefits to patients of the three intervention arms will be measured in two ways. Public preferences will be elicited regarding the value they place on different recall strategies using a discrete choice experiment (DCE) (see economic analysis). The DCE will be administered to a separate sample of the public obtained from electoral rolls over the course of the trial. Benefits are also measured in terms of QALYs (see above).

### Analysis plan

### Statistical analyses

The trial outcomes will be compared between the three trial arms using generalized linear models adjusting for the minimisation covariates and other covariates felt to be of prognostic importance. Statistical significance will be at the 2.5% level and corresponding confidence intervals will be derived. All participants will remain in their allocated group for analysis (intention to treat). Subgroup analyses will explore the possible effect modification of a number of factors including age, social class, residence in a fluoridated area, dentist characteristics (e.g. professional engagement, workplace stress) all using stricter levels of statistical significance (*p* < 0.01). All trial analyses will be according to a statistical analysis plan that will be agreed in advance by the Trial Steering Committee (TSC). The Data Monitoring and Ethics Committee (DMEC) will meet at 9, 24, 36 and 48 months to review progress and recommend any responses to divergences from planned trial design.

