#### Recall strategy allocation

Prior to randomisation, all patient participants will be clinically examined by their dentist to determine suitability for randomisation to the 24 m recall arm. A detailed risk assessment is not part of this suitability examination and the decision made will be based on current practice, with routine examination criteria and record keeping.

Randomisation will be organised within two strata depending on the recruited participant’s suitability to enter the 24 m arm:

1) Twenty-four month recall versus risk-based recall versus six month recall;

2) Risk-based recall versus six month recall.

Randomisation to trial arms will be carried out using the automated central randomisation service at the Centre for Healthcare Randomised Trials (CHaRT) at the University of Aberdeen, with 24 h access by telephone. Allocation will take place after the suitability examination. Eligible participants will be randomised in equal proportions within each of the two strata according to a minimisation algorithm including dentist, age, filled teeth - FT (FT ≤ 8 or FT > 8 [8]) and absence of gingival bleeding on probing. There will be separate, identical algorithms for the two strata. The design is summarised in the graphic below (Fig. 2).

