### Sample size

An exploratory trial in a similar population reported 35% of gingival sites were bleeding on probing (standard deviation of 25%) [16]. The Cochrane review of periodontal instrumentation (PI) suggested that six monthly PI versus no PI reduces bleeding sites by 15% [17]. The recall interval would be expected to produce an effect lower than this given that the majority of participants in all arms will still receive PI at some time during follow up. Assuming either risk-based versus 24 m or six month versus 24 m could reduce/increase the proportion of sites bleeding by 7.5%, a study with 235 in each arm could detect such a difference with 90% power at 5% significance, and likewise detect a difference of 0.3 of the standard deviation of the OHIP-14 or any other global measure of OHRQoL. For the caries clinical outcome, assuming a standard deviation of 3.5 a study with 235 participants per arm could detect a shift in white spots lesions (from 3.3 to 4.2) at 80% power and 5% significance [18].

We can combine the two strata, without introducing bias, to estimate this comparison. We anticipate smaller effect sizes for the six month versus risk-based recall comparison than six monthly versus 24 monthly given that many of the participants in the risk-based group will be seen more frequently than 24 m. A study with 750 participants in each arm could detect a difference in bleeding scores of 4.5% at least 90% power and 5% significance level, and likewise detect a difference of 0.17 of the standard deviation of the OHIP-14. For the caries clinical outcome, assuming a standard deviation of 3.5 a study with 750 participants per arm could detect a 20% relative shift in white spot lesions from 3.3 to 3.9 at 90% power and 5% significance [18].

Although there is no reason to be concerned about contamination effects in this trial or clustering by dentist, the sample size has been conservatively estimated such that if contamination occurred with 15% of the control participants or the intra cluster correlation was 0.03, the study would still have 80% power to detect the hypothesised changes in the bleeding score. Our sample size calculations indicate we need to randomise 705 participants to stratum 1 (235 in each arm) and 1030 to stratum 2 (515 in each arm).

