### Ethical considerations

The trial will be coordinated by TOD in the University of Dundee and CHaRT in the University of Aberdeen – both centres with experience of multicentre trials, cognisant of the implications of research governance and other legal frameworks for the conduct of trials. Informed signed consent will be obtained from the trial participants who will be given sufficient time to accept or decline involvement and are free to withdraw from the study at any time. The design of the study ensures that adults for whom a 24-month recall interval may be detrimental are not put at risk of allocation to this group. It will be made clear to participants and dentists that participants may attend at any time if there is a need for a dental appointment between recall visits. No dental treatment including referral to specialist services will be withheld from participants as a result of taking part in the trial.

This is not classed as a trial of any investigational medicinal products or procedures, and so does not come under EU Clinical Trials Directive. We will continue to conduct the study to the standards required by the NHS Universities Research Governance Framework as well as all other applicable legal, ethical and regulatory requirements.

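### The analysis text neither confines the 24-month contrasts to stratum 1 nor names randomisation stratum as a covariate, although the 24-month arm exists only in stratum 1

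*Protocol article*

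**What the plan says.** All references are to the protocol article.

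- **Recall strategy allocation.** "Randomisation will be organised within two strata depending on the recruited participant’s suitability to enter the 24 m arm". Stratum 1 is "Twenty-four month recall versus risk-based recall versus six month recall"; stratum 2 has only the risk-based and six-month arms. Allocation is equal within each stratum. The minimisation factors are dentist, age, filled teeth and absence of gingival bleeding. Stratum is not among them, because it sits above the minimisation: "There will be separate, identical algorithms for the two strata".
- **Statistical analyses.** "The trial outcomes will be compared between the three trial arms using generalized linear models adjusting for the minimisation covariates". The same sentence allows further covariates that are thought to be prognostic, without listing them. All participants stay in their allocated group, and the detail is deferred to a statistical analysis plan agreed by the steering committee. Stratum is not mentioned.
- **Estimation of costs, Estimation of benefits, Estimation of cost-effectiveness.** Cost differences are adjusted for baseline characteristics, with the minimisation variables as the example. If baseline EQ-5D differs, QALYs are regressed on baseline EQ-5D and arm, with no other term. The cost-effectiveness section compares 24-month with six-month recall from differences between arms. None of these sections mentions stratum.
- **Sample size.** The 24-month contrasts are sized at 235 per arm and the six-month versus risk-based contrast at 750 per arm. The totals are 705 in stratum 1 (235 per arm) and 1030 in stratum 2 (515 per arm). Between the two calculations stands "We can combine the two strata, without introducing bias, to estimate this comparison".
- **Ethical considerations.** The design ensures that "adults for whom a 24-month recall interval may be detrimental are not put at risk of allocation to this group".

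**The concern.** Randomisation compares 24-month recall with the other strategies only inside stratum 1. The six-month and risk-based arms also contain stratum 2 participants, whom the dentist judged unsuitable for 24 months. The Ethical considerations section explains that this judgement is about possible detriment, so stratum may well be related to outcome. A model fitted to all participants, with arm and covariates but no stratum term, would set a 24-month arm drawn wholly from one population against comparators drawn mostly from another. Two of the three pairwise contrasts would then mix the effect of the recall interval with suitability for it. The same applies to the cost and QALY comparisons involving 24-month recall.

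Six-month versus risk-based recall is not affected, because allocation between those two arms is equal in both strata and pooling them is sound.

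The Sample size wording adds to the difficulty. The sentence on combining strata directly follows the 24-month calculation. Only the text after it shows that it refers to six-month versus risk-based recall.

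**Working it through.** **1. Reproduce the plan's figures.** Inputs from Sample size: SD 25 points, difference 7.5 points, 90% power, 5% significance (taken as two-sided).

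n per arm = 2 × (1.960 + 1.282)² × 25² / 7.5² = 234 after rounding up, against a stated 235. Power at 235 per arm is 90.2%.

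Arms: 705/3 = 235 and 1030/2 = 515, and 235 + 515 = 750. So the 235 is exactly the stratum 1 arm size, and the 750 is the two strata combined. With 750 per arm, power for 4.5 points is 93.6%, consistent with the stated minimum of 90%.

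**2. Composition if the strata are pooled.** Stratum 2 makes up 515/750 = 68.7% of the six-month arm and of the risk-based arm, and 0% of the 24-month arm.

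**3. Bias with no stratum term.** Let D be the difference in mean bleeding between strata that remains after covariate adjustment. The documents do not give D; 1 to 10 points is an assumption. The size of the bias in either 24-month contrast is 0.687 × D.

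**4. False-positive rate with no true effect.** SE = 25 × √(1/235 + 1/750) = 1.87 points. With b = 0.687 × D, the two-sided rate at 5% is 1 − Φ(1.96 − b/SE) + Φ(−1.96 − b/SE).

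| D (assumed, points) | Bias (points; target 7.5) | False-positive rate (nominal 5%) |
|---|---|---|
| 1 | 0.7 | 6.6% |
| 2 | 1.4 | 11% |
| 5 | 3.4 | 45% |
| 10 | 6.9 | 96% |

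The 5% level matches the Sample size section. At the 2.5% level given under Statistical analyses, the rates for D = 5 and D = 10 are 34% and 92%.

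**5. Simulation check.** 1000 trials per value of D, planned arm sizes, no true arm effect, stratum 2 given the higher mean, no covariates other than stratum. Mean 24-month minus six-month estimate:

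| D | No stratum term | Stratum term | Stratum 1 only |
|---|---|---|---|
| 2 | −1.4 | 0.0 | −0.1 |
| 5 | −3.6 | −0.2 | −0.2 |
| 10 | −6.9 | 0.0 | 0.0 |

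**6. Why restriction is safer than a stratum term alone.** A model with only arm and stratum terms assumes that the six-month versus risk-based effect is the same in both strata. If it differs by d, the pooled estimate of that effect departs from its stratum 1 value by 0.687 × d. Half of this falls on each of the two arms, so each 24-month contrast shifts by about 0.687/2 = 0.34 × d. Risk-based intervals run from three to 24 months according to risk, so d need not be zero. Restriction to stratum 1 removes this dependence.

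**The case against.** The strongest reply has three parts.

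First, a reader who stops at the minimisation covariates might infer that the model adjusts for those alone. The sentence goes on to allow other prognostic covariates, and stratum is an obvious candidate. In the simulation above, a stratum term by itself brings the bias to about zero. This stands: the protocol does not exclude stratum.

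Second, the Sample size section already separates the contrasts. It sizes the 24-month comparisons on the stratum 1 arms and uses the combined 750 for six-month versus risk-based recall. A comparison of 235 with 750 appears nowhere in the protocol. This also stands, and it is good evidence of intent.

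Third, this is a condensed article, and analysis sets and covariate lists are commonly left to the analysis plan. That is fair as far as missing detail goes, and the plan may well settle the matter. However, the article does state a three-arm comparison, and it writes out a QALY regression whose terms are listed without stratum. Neither matches the randomisation described in the same article. A factor that determines which arms are possible should also not depend on whether it is felt to be prognostic.

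On size, bleeding status, filled teeth, age and dentist would absorb part of any difference between strata, so D has to be read as a residual. The suitability examination involves no detailed risk assessment, which may also keep D small.

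**Conclusion.** The point holds as an inconsistency of wording between the analysis sections on one side and the randomisation and sample size on the other. It is worth correcting because the correction is free and the possible distortion is not small. The bias of 0.687 × D arises only if strata are pooled and stratum is left out. Its range, about 0.7 to 6.9 points against a 7.5-point target, rests on an assumed D of 1 to 10 points with a common SD of 25.

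A reader might infer that the trial will in fact produce biased 24-month contrasts. The documents do not support that: the 235 per arm points to a stratum 1 comparison, and the final model is not shown. A reader might also infer that the bias would favour 24-month recall. That requires stratum 2 to have worse outcomes after adjustment, and no figure in the documents establishes it. Nor is the absence of stratum from the subgroup factors a defect, because that list is given as examples and is open.

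**What to change.** Add to Statistical analyses, and carry into the analysis plan:

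1. Six-month versus 24-month and risk-based versus 24-month recall are estimated in stratum 1 participants only, in the groups to which they were allocated.
2. Six-month versus risk-based recall pools both strata, with randomisation stratum as a covariate.
3. The cost, QALY and cost-effectiveness comparisons follow the same rule.

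In Sample size, name six-month versus risk-based recall in the sentence on combining strata.

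The cost is a few sentences. Stratum is recorded for everyone before allocation, so no new data are needed and the intention-to-treat principle is unaffected. Restriction gives the 235 versus 235 comparison that the trial was sized for (90.2% power at 5%). Against an unadjusted pooled comparison the SE rises from 1.87 to 25 × √(2/235) = 2.31 points, but the planned power already allows for that.

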#### Economic outcomes

NHS costsPatient incurred costsGeneral population preferences, willingness to payNet benefits (Benefits – costs)Generic Quality of Life, measured using the EQ-5D-3 LQuality adjusted life years (QALYs)Incremental cost per QALY gained

There are two primary outcomes: the primary clinical outcome is periodontal disease as measured by gingival bleeding, and the primary patient centred outcome is oral health-related quality of life as measured by the Oral Health Impact Profile-14 (OHIP-14). These are the outcomes that the study is powered at 80% to detect meaningful changes. Other measures are collected as secondary outcomes. Given the complex intervention and the unknown correlation between the two different dimensions of the study (patient and clinical), the study will not correct the *p*-value for multiplicity of tests.

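### Analysis at 2.5% with sidedness unstated, power at 5%, and no multiplicity correction claimed: if 2.5% is two-sided these do not describe one design, and the stated powers do not hold

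*Protocol article*

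**What the plan says.** Three places in the protocol article bear on the significance level.

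- **Statistical analyses:** "Statistical significance will be at the 2.5% level and corresponding confidence intervals will be derived". Sidedness is not given, 2.5% is not explained, and the level of the intervals has to be inferred.
- **Sample size:** every level named is 5%. For the comparisons with the 24-month arm, "a study with 235 in each arm could detect such a difference with 90% power at 5% significance", the difference being 7.5 points in either direction; the same power is claimed for 0.3 SD of OHIP-14. For six-month versus risk-based recall, with 750 per arm, the claim is that the trial "could detect a difference in bleeding scores of 4.5% at least 90% power and 5% significance level"; the same power is claimed for 0.17 SD of OHIP-14. The section adds that 80% power for bleeding would survive 15% contamination of controls or an intracluster correlation of 0.03.
- **The paragraph on the two primary outcomes, at the end of Economic outcomes:** bleeding and OHIP-14 are both primary. "These are the outcomes that the study is powered at 80% to detect meaningful changes", and "the study will not correct the *p*-value for multiplicity of tests", because the intervention is complex and the correlation between the two outcomes is unknown.

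**The concern.** With two primary outcomes, 2.5% is what an even split of 5% would give. The Statistical analyses section therefore looks as if it applies the correction that the primary-outcomes paragraph disclaims, while the sample size was worked out as if there were none. Nothing in the article resolves this.

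Two things are at stake. First, a primary result with a two-sided p-value between 0.025 and 0.05 would be significant at the level the trial was sized for and not at the level named for the analysis, and it is open whether 95% or 97.5% intervals are to be reported. Second, if the test is two-sided at 2.5%, the published power figures do not belong to it.

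**Working it through.** **Inputs** (all from Sample size): SD of bleeding 25 percentage points; differences 7.5 points (235 per arm) and 4.5 points (750 per arm, which is 235 + 515 over the two strata); OHIP-14 differences 0.3 SD and 0.17 SD.

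**Formula.** For two equal arms of n and standardised difference d, power ≈ Φ(d·√(n/2) − z), with z = 1.960 for two-sided 5% and z = 2.241 for two-sided 2.5%.

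**Noncentrality, d·√(n/2)**
- 7.5/25 = 0.30, n = 235: 0.30 × √117.5 = 3.252. OHIP-14 at 0.3 SD gives the same value.
- 4.5/25 = 0.18, n = 750: 0.18 × √375 = 3.486
- 0.17 SD, n = 750: 0.17 × √375 = 3.292

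**Power: the plan's own level first, then 2.5%**

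| Comparison | Stated | Two-sided 5% | Two-sided 2.5% | n per arm for 90%, at 5% / at 2.5% |
|---|---|---|---|---|
| 7.5 points, or 0.3 SD, 235 per arm | 90% | Φ(1.292) = 90.2% | Φ(1.011) = 84.4% | 234 / 276 |
| 4.5 points, 750 per arm | at least 90% | Φ(1.526) = 93.7% | Φ(1.244) = 89.3% | 649 / 767 |
| 0.17 SD of OHIP-14, 750 per arm | at least 90% | Φ(1.332) = 90.9% | Φ(1.051) = 85.3% | 728 / 859 |

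The t-test calculation agrees to within 0.3 percentage points (90.1%, 93.6%, 90.8% at 5%; 84.2%, 89.3%, 85.3% at 2.5%). The near-exact match of 234 with 235 shows that the design was computed at two-sided 5% (numerically the same as one-sided 2.5%).

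**Detectable difference** at 90% power, two-sided 2.5%, 235 per arm: (2.241 + 1.282) × 25 × √(2/235) = 8.1 points, against 7.5 stated.

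**Contamination fallback.** The article gives no model, so I assume that 15% contamination multiplies the effect by 0.85.
- 235 per arm: 3.252 × 0.85 = 2.764, giving 78.9% at 5% and 69.9% at 2.5%.
- 750 per arm: 3.486 × 0.85 = 2.963, giving 84.2% at 5% and 76.5% at 2.5%.

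**Intracluster correlation fallback.** This needs a cluster size that is not stated. Take the planned 50 dentists and divide n by 1 + (m − 1) × 0.03. With m counted per arm, power falls from 87.0% to 80.1% (235 per arm) and from 83.3% to 75.3% (750 per arm). With m counted over both compared arms, it falls from 82.8% to 74.7% and from 72.2% to 62.1%. The range is too wide to support one figure.

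**Multiplicity.** Two outcomes at 2.5% each give a family-wise bound of 2 × 2.5% = 5%. Two outcomes over three pairwise arm comparisons are six tests, with a bound of 6 × 2.5% = 15%. A 2.5% level therefore covers the two outcomes at most.

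**The case against.** Several points on the other side have weight.

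*One-sided 2.5%.* On this reading the powers are unchanged, 95% intervals follow, and nothing conflicts with making no correction. It cannot be excluded, but the article does not say it, and the bleeding difference is framed in both directions, which points to two-sided tests.

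*Only one section sets a threshold.* Statistical analyses names the decision level, Sample size records planning assumptions, and the primary-outcomes paragraph names no level. That is right. The defect is an unexplained level that does not match the planning, rather than two rival decision rules.

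*The recruitment target is larger.* The Abstract plans 2372 participants, against 705 + 1030 = 1735 in Sample size. If 2372 splits in the same proportions (an assumption), 15% loss leaves 2372 × 0.85/1735 = 1.162 times the stated arms, about 273 and 872. Power at two-sided 2.5% is then 89.7%, 93.5% and 90.5% for the three rows of the table. Adding the 10% loss of dentists leaves about 246 and 784, with 86.1%, 90.7% and 87.0%. If instead 235 and 750 are numbers randomised and 15% are lost, about 200 and 638 remain, with roughly 78%, 83% and 79%. So a reader might infer that the trial as run is underpowered. The article does not support that, because the analysed number is not settled. What stands is that the power stated for 235 and 750 per arm does not hold at two-sided 2.5%.

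*The 80% statement.* A reader might see a contradiction between 80% in the primary-outcomes paragraph and 90% in Sample size. Sample size itself gives 80% as a floor under contamination or clustering, and the unadjusted powers at 2.5% (84% to 89%) still exceed 80%.

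*The reason for not correcting.* An even split of 5% is valid under any correlation, so unknown correlation does not prevent it. The split is conservative when outcomes are correlated, however, and whether to correct across a clinical and a patient-centred outcome is partly a judgement. I do not count the choice as an error.

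**Conclusion.** The inconsistency is real. If 2.5% is two-sided, the level for analysis, the level for power and the statement on multiplicity do not describe one design.

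At the stated arm sizes the loss is about 6 percentage points for the 24-month comparisons (90% to 84%) and for OHIP-14 at 0.17 SD (91% to 85%). For the 4.5-point bleeding comparison it is about 4 points, and the result of 89% misses the stated minimum of 90% only narrowly. The bleeding fallback of 80% drops to about 70% and 76%, but only under the assumed 0.85 scaling, on which 235 per arm already reaches 80% at 5% only by rounding.

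It is tempting to conclude that 2.5% is a deliberate split of 5% and that the no-correction sentence is the slip. The article does not show which of the statements is wrong, and even a deliberate split would leave the three arm comparisons uncorrected. Because the threshold applies to both primary outcomes, it should be settled before unblinded results are seen.

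**What to change.** State one significance level for the primary outcomes, its sidedness, and the matching interval level: 97.5% if the test is two-sided at 2.5%, 95% if it is one-sided at 2.5%. Restate the power in Sample size at that level, for the number expected to be analysed after losses, and say how contamination was modelled for the fallback.

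- **If two-sided 2.5% is kept:** reword the primary-outcomes paragraph to say that the level splits 5% over the two primary outcomes and that the three pairwise arm comparisons remain uncorrected. Simply deleting the no-correction sentence would hide that second part. For 235 and 750 analysed per arm, the powers to print are 84% (90% for 8.1 points), 89% and 85%.
- **If 5% was intended:** correct the level in Statistical analyses. The no-correction sentence and the stated powers can then stand.
- **If 2.5% was meant as one-sided:** say so. The stated powers hold.

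The 80% line in the primary-outcomes paragraph need not change on the unadjusted figures.

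The cost is wording only, with no extra participants. If two-sided 2.5% is kept, the power stated for 235 and 750 per arm becomes less favourable.
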